## Abstract

**Background:**

The mechanism of the long-lasting effect and the relationship between the long-lasting effect and the *deqi* sensation, which is the key of achieving the acupuncture effect, has not been well investigated. This trial focuses on investigating the possible central mechanism of the long-lasting effect influenced by the *deqi* sensation.

**Methods:**

A randomized controlled functional brain imaging trial is currently being conducted in Sichuan, China. In total 105 functional dyspepsia (FD) patients will be allocated into three groups: an acupuncture with *deqi* group, an acupuncture without *deqi* group, and a wait-list group. This trial will include a 2-week baseline period, a 4-week treatment period, and a 4-week follow-up period. During the 4-week treatment, patients in two acupuncture groups will receive 20 sessions of acupuncture treatment with or without *deqi*. The Nepean Dyspepsia Index (NDI) and the short form Leeds Dyspepsia Questionnaire (SF-LDQ) will be used to evaluate the clinical efficacy of acupuncture treatment at baseline, the end of treatment, and the end of the follow-up. Functional magnetic resonance imaging (fMRI) scans will be performed to detect cerebral functional changes in 25 patients in each group at three time points mentioned above. The clinical data and fMRI data will be analyzed, respectively. Correlation analysis will be conducted to investigate the relationship between cerebral functional changes and symptom improvement.

**Discussion:**

The results of this trial will allow us to compare the changes of acupuncture therapeutic effect at three time points (the baseline vs. the end of treatment vs. the end of follow-up), and investigate the potential central mechanism of the long-lasting effect influenced by acupuncture with *deqi*. This trial aims to re-identify the long-lasting effect of acupuncture and investigate its central mechanism, and to further explore the central influence of *deqi* sensation on the long-lasting effect.

**Trial registration:**

Chinese Clinical Trial Registry, IDF: ChiCTR-IOR-15006523. Registered on 5 June 2015.

**Electronic supplementary material:**

The online version of this article (10.1186/s13063-018-2742-0) contains supplementary material, which is available to authorized users.

## Background

The long-lasting effect of a treatment, also called the “long-term effect,” is the perception of a curative effect for a period of time after treatment cessation. It has been widely found following observation after medical therapy [1–3]. For acupuncture treatment, the long-lasting effect is considered as one of the most important features in its therapeutic effect, which has been recorded in classical ancient Chinese books and proved by multiple modern clinical trials [4–10]. The long-lasting effect has been reported in trials of acupuncture for treating migraine [10], chronic headache [5], primary insomnia [8], tinnitus [9], etc. Our previous study found that, compared with sham acupuncture, verum acupuncture may be associated with long-term reduction in migraine recurrence [10]. Furthermore, this long-lasting effect is considered to be closely related to the *deqi* sensation, the key of achieving acupuncture efficacy [11]. In one of our previous randomized clinical trials (RCTs) we found that acupuncture on real acupoints presented persistent effect in the follow-up compared with acupuncture on sham acupoints in patients with functional dyspepsia [4]. However, the central mechanism of the long-lasting effect of acupuncture remains unknown, and its influencing factors have not been well studied.

Functional dyspepsia (FD) is defined as the presence of early satiation, postprandial fullness, epigastric pain, or epigastric burning in the absence of an organic, systemic, or metabolic disease that could explain the symptoms according to the Rome III consensus [12]. It is one of the most common categories in functional gastrointestinal disorders (FGID). In Sweden, the prevalence of FD is between 11 and 20% [13]. In Asia, it ranges from 8 to 23% [14]. Although FD is not life-threatening, it significantly influences quality of life (QOL) [15] and leads to high medical costs [16]. Nowadays, many approaches, such as daily proton pump inhibitors (PPI), tricyclic antidepressants, anti-nociceptive agents, and prokinetic agent have been used to treat FD [17–21], but the therapeutic effect is unsatisfactory due to its multi-factor pathology. As a result, more and more patients tends to seek complementary and alternative methods.

We design a randomized controlled functional brain imaging trial with a 10-week observation period, aiming at: (1) re-identifying the long-lasting effect of acupuncture treatment for FD by comparing the changes of therapeutic effect at three time points (the baseline vs. the end of treatment vs. the end of follow-up); (2) investigating the central mechanism of the long-lasting effect of acupuncture; and (3) exploring the influence of the *deqi* sensation on the long-lasting effect and its potential central mechanism.

## Methods and design

### Study design

This is a parallel-group, randomized controlled study. One hundred and five FD patients will be included and randomized with equal allocation to one of the three groups: acupuncture with *deqi* group, acupuncture without *deqi* group, and the wait-list group. Among 35 patients in each group, 25 participants will be selected randomly to undergo functional magnetic resonance imaging (fMRI) scans. This trial will include a 2-week baseline period, a 4-week treatment period, and a 4-week follow-up period. During the 4-week treatment, patients in two acupuncture groups will receive 20 sessions of treatments puncturing with or without *deqi*, while the wait-list group will not receive acupuncture treatment. Both the outcome assessments and fMRI scans will be performed at three time points including: the baseline, the end of the acupuncture treatments, and the end of follow-up (Figs. 1 and 2). This trial is reported in accordance with the Standard Protocol Items: Recommendations for Intervention Trials (SPIRIT) guidelines [22] (Fig. 2; Additional file 1).

**Fig. 1 Fig1:**
[figure not shown]
Study schedule for data collection. The informed consent and examination will be conducted after recruitment. Matched functional dyspepsia (FD) patients will be then randomized into three groups, where two acupuncture groups will receive treatment. Both clinical outcomes and functional magnetic resonance imaging (fMRI) scans will be performed at three time points including: the baseline, the end of acupuncture treatments, and the end of follow-up. Adverse events will be recorded in the case report at any time during the study. a. *NDI* Nepean Dyspepsia Index, *LDQ* Leeds Dyspepsia Questionnaire, *SAS* Self-Rating Anxiety Scale, *SDS* Self-Rating Depression Scale, *BAI* Beck Anxiety Inventory, *BDI* Beck Depression Inventory, *VAS* Visual Analog Scale

**Fig. 2 Fig2:**
[figure not shown]
Standard Protocol Items: Recommendations for Interventional Trials (SPIRIT) schedule of the trial. The present study is a randomized controlled functional brain imaging trial. One hundred and five functional dyspepsia (FD) patients will be included and randomized equally to one of the three groups: the acupuncture with *deqi* group, the acupuncture without *deqi* group, and the wait-list group. Among 35 patients in each group, 25 participants will be selected randomly to receive fMRI scans. This trial will include a 2-week baseline period, a 4-week treatment period and a 4-week follow-up period. During the 4-week treatment, patients in two acupuncture groups will receive 20 sessions of treatments, puncturing with or without *deqi*, while the wait-list group will not receive acupuncture. Both the outcome assessments and the fMRI scans will be performed at three time points: baseline, end of acupuncture treatments, and the end of follow-up. The central mechanism of the long-lasting effect and the central role of *deqi* on this effect will be analyzed after data collection

### Sample size

According to our previous study, Nepean Dyspepsia Index (NDI) scores of FD patients decreased by 12.2 points after acupuncture and by 7.8 points after sham acupuncture [23]. In this study, we anticipated a reduction of NDI score by 12 points after acupuncture with the *deqi* sensation and a reduction by 8 points after acupuncture without the *deqi* sensation, and we anticipated a reduction by 4 points in the wait-list control due to regression to the mean effect. With *α* = 0.05, 1 − *β* = 0.8, and a standard deviation of 10, we needed at least 96 participants in total. Considering a dropout rate of 10%, a total of 105 participants will be included in this trial. According to the sample size of previous blood-oxygenation-level-dependent fMRI (BOLD-fMRI) studies, 20 subjects is the reasonable sample size with stable statistical effect [24, 25]. Considering the dropout rate and loss of data due to head motion during fMRI scans, 25 participants from each group will receive fMRI scans in this study.

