### Interventions

The acupoints used in the study include unilateral *Zhongwan* (CV12) and bilateral *Zusanli* (ST36) (Fig. 3). The combination of CV12 and ST36 is commonly used for treating FD, and has been used in our previous studies [29].

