#### Acupuncture without the *deqi* group

To avoid the *deqi* response, no needle manipulation will be performed after the perpendicular insertion.

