### Needle sensation evaluations

Participants in the two acupuncture groups will be asked to fill the needle sensation evaluation form after receiving each acupuncture treatment. The form is based on the Chinese version of modified Massachusetts General Hospital Acupuncture Sensation Scale (C-MASS) [37, 38], and its validity and reliability have been examined [38, 39]. In the form, the Visual Analog Scale (VAS) [40] is selected to quantitatively evaluate the *deqi* sensation after each acupuncture treatment. This is a 10-point scale with anchor words “none” (no score), “mild” (about two scores), “moderate” (around five scores), “severe” (almost eight scores), and “unbearable” (nearly ten scores) spaced along the continuum. The scale will be used to access evaluate the *deqi* sensations (including soreness, numbness, fullness, heaviness, aching), respectively. Moreover, if the scale does not completely describe the needle sensations that subjects experienced, subjects can add what they feel in a blank row below the scale.

Since some participants were sensitive while some were not, both acupuncture groups’ participants will be re-divided into the “actual *deqi* group” and “actual without *deqi* group” according to the median of the mean needle sensation score across 20 times treatment. Then the “actual *deqi* group” and “actual without *deqi* group” will be compared with both clinical data and fMRI data.

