### *Deqi* may play an essential role in achieving the long-lasting effect for its definite influence on acupuncture effect

The long-lasting effect, as one of the most commonly phenomenon and important feature of acupuncture effect, refers to the perception of a curative effect for a period of time after termination of acupuncture treatment. It has been recorded in a number of ancient Chinese medical books and reported in many clinical trials such as acupuncture treatment for migraine [7], FD [4], cervical spondylosis [41], chronic pain in the knee joints [42], and others [5, 6]. For example, in a systematic review including 13 studies on chronic pain in knee joints, three of them found that the acupuncture efficacy still remained in the following 6 to 12 months after treatment [42]. Our previous multicenter clinical trials on acupuncture treatment for FD also demonstrated that the effects of puncturing on acupoints were not only significantly different from those on non-acupoints at the end of 4 weeks’ treatment, but also in the 4 weeks and 12 weeks after the termination of treatment [4]. All the above indicated the existence of the long-lasting effect and its importance in keeping acupuncture efficacy.

*Deqi,* also called the arrival of *qi*, or the needle sensation, is a series of multidimensional and intense sensations including numbness, soreness, distention, heaviness, and dull pain, etc. that patients experience during acupuncture stimulation [43]. A great amount of ancient acupuncture classics recorded that “ the achievement of acupuncture effect depends on the *qi* arrival” (“*Huangdi Neijing*,” *The Inner Canon of Huangdi*), and “the quicker the *qi* arrives, the faster the acupuncture effect acquires” (“*Biao You Fu*,,” *a Poetic Prose on the Elucidation of Acupuncture*). Modern clinical trials have considered that *deqi* plays an essential role in the process of achieving the acupuncture effect [37, 44–47]. For example, a study on Bell’s palsy found that acupuncture with *deqi* can induce a greater therapeutic effect, and stronger intensity of *deqi* was associated with better therapeutic effects [47].

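### The 4-point deqi difference appears to be borrowed from a real-versus-sham result, is not justified for a same-acupoint comparison, and is not protected by the stated 80% power

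*Protocol article*

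**What the plan says.** The Sample size section starts from one earlier result: "Nepean Dyspepsia Index (NDI) scores of FD patients decreased by 12.2 points after acupuncture and by 7.8 points after sham acupuncture". The next sentence sets the planning values: "a reduction of NDI score by 12 points after acupuncture with the *deqi* sensation", "a reduction by 8 points after acupuncture without the *deqi* sensation" and "a reduction by 4 points in the wait-list control due to regression to the mean effect". With a standard deviation of 10, alpha 0.05 and power 0.8, it arrives at 96 participants, raised to 105 for dropout. It does not name the test.

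The Interventions section gives one set of points for the whole trial ("The acupoints used in the study include unilateral" CV12 and bilateral ST36), with no separate set for either needling arm. The section on the without-deqi group changes only the technique: "no needle manipulation will be performed after the perpendicular insertion".

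The third aim in the Background is the influence of deqi on the long-lasting effect. The Clinical data analysis section names with versus without deqi as the comparison made primarily, using a repeated measures model over three time points.

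**The concern.** The figures 12 and 8 look like 12.2 and 7.8 rounded. If so, a difference between acupuncture and sham acupuncture has been relabelled as a difference between needling with and without deqi. These need not be the same. In this trial both needling arms share the points, the insertion and the number of sessions, so anything that point location contributes cancels out of the deqi contrast.

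The protocol itself holds that location matters. Its Discussion says of an earlier functional dyspepsia trial that "the effects of puncturing on acupoints were not only significantly different from those on non-acupoints". It also expects the sensation felt to vary between patients ("Since some participants were sensitive while some were not") and plans to regroup both needling arms by actual sensation. The planning values make no visible allowance for this.

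At stake is the third aim. If the real difference between these two arms is smaller than 4 points, a null result becomes still more likely, and it could be misread as showing that deqi has no influence.

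**Working it through.** **Inputs.** Mean reductions 12, 8 and 4, SD 10 and alpha 0.05 come from Sample size; the two-sided test from Clinical data analysis; equal allocation from Study design. I take SD 10 as the SD of the change score, which the article does not state. Values for the without-deqi mean other than 8 are my assumptions, because the article gives no response for unmanipulated needling at these points.

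**1. Reproduce the plan's 96.** For a one-way three-group F test, the noncentrality is λ = n × Σ(mean − grand mean)² / SD². The grand mean is 8, so the sum of squares is 16 + 0 + 16 = 32.
- n = 32 per group: λ = 32 × 32 / 100 = 10.24, power 0.812.
- n = 31 per group: power 0.798.

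So 32 × 3 = 96, matching the article. A 12 versus 8 comparison at 80% power needs 99 per arm two-sided or 78 one-sided, and neither gives 96 in total. The 80% therefore belongs to the overall three-group test.

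**2. Change only the without-deqi mean, overall test, 32 per group.** With means 12, 10 and 4 the grand mean is 8.67 and the sum of squares is 11.11 + 1.78 + 21.78 = 34.67. Then λ = 32 × 34.67 / 100 = 11.09, power 0.844. At 9 and 11 the power is 0.82 and 0.88. The group size needed for 80% falls from 32 to 31, 29 and 27 at means of 9, 10 and 11. The 12 versus 4 spread drives this test. A middle mean of 8 is its least favourable value, so moving that mean off 8 in either direction raises the overall power.

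**3. The deqi contrast itself, 32 per arm.** The standard error of the difference is 10 × √(2/32) = 2.5 and the noncentrality is difference / 2.5. The critical t on 62 degrees of freedom is 1.999.

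| Without-deqi mean | Difference | Noncentrality | Power | n per arm for 80% |
|---|---|---|---|---|
| 8 (plan) | 4 | 1.6 | 0.35 | 99 |
| 9 | 3 | 1.2 | 0.22 | 175 |
| 10 | 2 | 0.8 | 0.12 | 393 |
| 11 | 1 | 0.4 | 0.07 | 1570 |

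The last column uses the normal approximation 2 × (1.960 + 0.842)² × SD² / difference².

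The 95% CI half-width is 1.999 × 2.5 = 5.0 points, wider than the assumed 4-point difference.

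**4. The other direction.** If the without-deqi mean were 7, the difference would be 5, the noncentrality 5 / 2.5 = 2.0 and the power about 0.50. By the normal approximation, 80% power needs a difference of about 2.80 × 2.5 = 7.0 points.

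**Limit.** These are single-time-point figures. The planned model is repeated measures, and the article gives no correlation from which to compute its power.

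**The case against.** A reader might infer that the 4 points are definitely overstated, with 8 a floor for the control response and 4 a ceiling for the deqi effect. The document does not support that.

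- The sham procedure in the study behind 12.2 and 7.8 (reference 23) is not described. The statements about sham points and non-acupoints in the Background and Discussion cite a different study (reference 4). If the reference 23 sham was needling without manipulation, 7.8 would be a fair proxy.
- Even if that sham used non-acupoints, it may have been manipulated and may have produced deqi. The new control arm would then keep the location but lose the deqi component, and its response could be lower than 7.8. Patients are hard to blind here, so expectation could also widen the contrast.
- The remark on sensitive participants covers both needling arms and does not quantify deqi in the control arm. Similar variation may already be present in the 12.2 versus 7.8 result.
- The link from 7.8 to 8 is implied by adjacency, not stated.

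All of this stands, and it leaves the sign of the error open. It does not supply a justification for 4 points in a same-acupoint comparison.

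It is also fair to say that most of the low power comes from sizing on the overall test: 35% is the figure when the 4 points are exactly right. Only the step down from 35% belongs to the borrowed value, and its size depends on an assumed control response. Finally, how to report and interpret a contrast is often left to an analysis plan, and the article already lists 95% CIs as descriptive statistics. The reporting part of the fix is therefore an addition that follows from the power figures, not a claim of omission.

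**Conclusion.** The point holds in this form: the 12 versus 8 assumption appears to be taken from a real-versus-sham result, while the trial compares two ways of needling the same points. The 4-point difference is not justified for that comparison and may be too large; how far it is off, and in which direction, cannot be determined from the document.

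The single 80% figure cannot reveal an error here. A without-deqi mean of 10 instead of 8 moves the overall power from 0.81 to 0.84 and the deqi contrast from 0.35 to 0.12. The conclusion about the contrast's power does not depend on the direction of the error: it is 35% at the plan's own 4 points and about 50% at 5.

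This rests on 32 evaluable patients per arm, SD 10 for the change score, a two-sided 0.05 t test at one time point, and my reading of 96 as the overall test, which the figures reproduce but the article does not state.

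**What to change.** In Sample size:
- State that the 8-point figure is borrowed from a sham control and may not apply to needling the same acupoints without manipulation. Do not describe it as a bound in either direction.
- State that the 80% refers to the overall three-group test.
- Give the power of the deqi contrast at 32 per arm as about 35%, 22%, 12% and 7% for differences of 4, 3, 2 and 1 points, with a 95% CI half-width of about 5.0 points, and name the single-time-point t test as the basis.

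In Clinical data analysis, say that the with versus without deqi contrast will be reported as an estimate with its 95% CI, and that a non-significant result will not be interpreted as absence of a deqi influence.

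The cost is wording only: no extra patients and no change to procedures. The downside is that the stated power for the main question becomes visibly less favourable.

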## Data analysis

### Clinical data analysis

The intention-to-treat analysis will be used for all allocated participants in the baseline. This study focuses on the lasting-effect of acupuncture, and the observed data will be used as the primary analysis and last observation-carried-forward (LOCF) analysis will be taken as a sensitivity analysis. Clinical outcome will be analyzed using SPSS 22.0 statistics software (IBM SPSS Statistics, IBM Corp, Somers, NY, USA). Data on Skewed distribution will be normalized. Means, standard deviations, and 95% confidence intervals (CIs) will be used to describe the continuous data.

The demographic and baseline characteristics among three groups will be compared using one-way analysis of variance (ANOVA). A *χ*^2^ test will be used for categorical variables. Due to the occurrence of self-healing tendency in FD, it is important to testify the existence of acupuncture effect. The clinical outcome NDI and SF-LDQ scores will be compared between the acupuncture group and the wait-list group among three time points by using the repeated measures ANOVA (two independent groups with repeated measures). Then, the acupuncture group with and without *deqi* at three time points will be primarily compared using repeated measures model.

A two-sided test will be used during the analysis, with a significance level of 0.05. The data will be analyzed by statisticians who are blinded to the test settings.

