### The quality control program is the precondition for the result reliability

To improve the result reliability of this study, we design the quality control program from the following four aspects: (1) patient selection for the influence of age and handedness on cerebral function and structure have long been investigated, this study restricts the subjects to age between 18 to 45 years and being right-handed for baseline homogeneity; (2) sample size to obtain stable statistical power; we include 35 patients in each group for clinical evaluation and 25 patients in each group for the central mechanism study; and (3) fMRI scan; all scans are performed in the morning with the same scanner and operator. Scans on female participants are performed during the same menstrual cycle. Moreover, during the 24 h before scanning, participants will be asked to maintain their regular lifestyle and avoid overexertion and staying up late. No permission with alcohol, tobacco, tea, and coffee. Before being scanned, the emotional state of each participant will be evaluated via the emotional state assessment scales. To exclude significant emotional changes, during the scan participants will be asked to close their eyes and use a blindfold and to plug their ears with earplugs, stay awake, and not to speak. The scan room keeps the temperature between 18 and 22 °C, with humidity greater than 60% and noise less than 150 dB; (4) acupuncture manipulation; the acupuncture treatment will be performed by two experienced acupuncturists using a standard operation procedure. The *Deqi* sensation will be evaluated and recorded with the VAS after each acupuncture treatment.

In conclusion, the long-lasting effect is an important feature in acupuncture efficacy, and *deqi* may be one vital factor in producing the long-term effect. This study is the first functional brain imaging study which focuses on exploring the central mechanism of the long-lasting effect and the central influence of *deqi* on this effect with strict quality control. The results may provide a new approach to investigate the mechanism of the long-lasting effect.

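### The sample size of 96 fits a three-group omnibus test, but only two-group efficacy comparisons are planned, and the with versus without deqi comparison has about 35% to 38% power on the plan's own figures

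*Protocol article*

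**What the plan says.** The Sample size section sets out three expected outcomes: "we anticipated a reduction of NDI score by 12 points after acupuncture with the *deqi* sensation", "a reduction by 8 points after acupuncture without the *deqi* sensation", and, for the third arm, "we anticipated a reduction by 4 points in the wait-list control due to regression to the mean effect". With alpha 0.05 and power 0.8 it then states "and a standard deviation of 10, we needed at least 96 participants in total", and adds: "Considering a dropout rate of 10%, a total of 105 participants will be included in this trial". Neither a test nor a comparison is named.

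The Clinical data analysis section applies a three-group ANOVA to baseline characteristics only. NDI and SF-LDQ are analysed in two steps, each with two groups. Acupuncture is first set against wait-list by repeated measures ANOVA. Then the arms with and without deqi "at three time points will be primarily compared using repeated measures model". Tests are two-sided at 0.05.

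The Control section gives the influence of deqi as the reason for the without-deqi arm, and the third aim in the Background depends on that contrast. The quality control part of the Discussion presents the numbers as "sample size to obtain stable statistical power; we include 35 patients in each group for clinical evaluation".

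**The concern.** A sample size carries its power only for the test it was derived from. Here three means go in, while the efficacy analyses compare two groups at a time. The three-group test gains most from the largest gap, 12 − 4 = 8 points between deqi and wait-list. The contrast that addresses deqi has an assumed gap of 12 − 8 = 4 points, half of that.

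The interpretation of the deqi result is at stake. Beside an unqualified 80%, a non-significant difference between the two acupuncture arms invites the conclusion that deqi makes no difference. If the real power is well under one half, that outcome is the more likely one even when the sponsor's assumptions are exactly right.

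**Working it through.** **Inputs.** From Sample size: mean reductions 12, 8 and 4; SD 10; alpha 0.05; power 0.8; N = 96, so 32 per arm; 105 randomised, so 35 per arm. From Clinical data analysis: two-sided tests and the two comparisons. From Study design: equal allocation.

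**1. Reproduce 96.** One-way F test, three groups:
- The grand mean is 8, and f = √[((12−8)² + (8−8)² + (4−8)²)/3] / 10 = √(32/3)/10 = 0.327.
- With noncentrality N·f², power is 79.8% at 31 per arm and 81.2% at 32 per arm.
- The smallest size reaching 80% is therefore 3 × 32 = 96, the plan's figure.

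The two-group calculations tried do not give 96. A 4-point difference needs 99 per group by the normal approximation, and an 8-point difference needs 25 per group. Pooled acupuncture versus wait-list (2:1) needs 99 in total by the normal approximation, or 102 by the exact t test.

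**2. Acupuncture versus wait-list.** Two-sample t test with noncentrality (difference/SD)/√(1/n₁ + 1/n₂):
- Both acupuncture arms pooled: mean (12+8)/2 = 10, difference 10 − 4 = 6. With 64 versus 32, noncentrality is 0.6/√(1/64 + 1/32) = 2.77 and power is 78%. With all randomised, 70 versus 35, power is 82%.
- Deqi arm alone: difference 8. With 32 per arm, noncentrality is 0.8 × √(32/2) = 3.2 and power is 88%. With 35 per arm it is 91%.

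**3. With versus without deqi.** Difference 4, SD 10 read as the SD of change, one time point:
- 32 per arm: noncentrality 0.4 × √(32/2) = 1.6; power 35.0%.
- 35 per arm: noncentrality 0.4 × √(35/2) = 1.67; power 37.8%.
- Size for 80% (normal approximation): 2 × (1.96 + 0.842)² × 10²/4² = 98.1, so 99 per arm; the exact t test gives 100.
- Difference detectable with 80% power at 32 per arm: about 7.1 points. Equivalently, a 4-point difference would need an SD of about 5.6.

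**4. Allow for the repeated measures.** The article gives no correlation, so these are assumed ranges. Suppose the 4-point difference holds at both post-baseline visits and the two changes, correlated ρ, are averaged. The SD becomes 10 × √((1+ρ)/2). At 32 per arm:

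| ρ | SD | Power |
|---|---|---|
| 1 | 10.0 | 35% |
| 0.7 | 9.2 | 40% |
| 0.5 | 8.7 | 44% |
| 0.3 | 8.1 | 50% |
| 0 | 7.1 | 61% |

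**5. Read SD 10 as a raw-score SD instead.** With baseline correlation r between 0 and 0.8, at 32 per arm and one time point:
- Baseline-adjusted analysis, SD 10 × √(1−r²): power 35% to 75%. Reaching an SD of 5.6 needs r of about 0.83.
- Unadjusted change scores, SD 10 × √(2(1−r)): power 20% to 70%.

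**The case against.** The best defence is that nothing was miscalculated. The 96 is exactly right for a three-group test, and the article never attaches the 80% to the deqi contrast. Both points stand: this is a mismatch between the test that was sized and the tests that are planned. A reader might infer that the article claims 80% power for with versus without deqi; it names no comparison. A reader might also infer that the 80% fits none of the planned tests. Step 2 shows otherwise, since acupuncture versus wait-list lies near or above 80% on either reading of the acupuncture group.

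The primary status of the deqi contrast rests on one adverb, and the third aim is worded as exploration. That is fair, and there is no formal declaration of a primary comparison. But the Control section justifies a whole arm by this question, so its precision matters whatever label it carries.

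The 35% is also one scenario, since it takes SD 10 as an SD of change and uses a single visit although a repeated measures model is planned. That stands too, and is why steps 4 and 5 give ranges. They moderate the shortfall without removing it: 80% would need, for example, a baseline correlation of about 0.83 under the raw-score reading, and the article states no such assumption.

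Finally, a reader might make something of 105 × 0.9 = 94.5 being below 96. It has no consequence, because 94.5 patients still give 80.5% for the three-group test.

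**Conclusion.** The point holds as a mismatch confined to the deqi contrast. The stated size and power belong to a three-group omnibus test that is not among the efficacy analyses. Acupuncture versus wait-list is roughly adequately powered. With versus without deqi, at the plan's own 4-point difference and SD 10 as the SD of change at one visit, has 35% to 38% power, with a detectable difference of about 7.1 points, nearly twice the one assumed. Averaging two visits gives about 40% to 50% at assumed correlations of 0.7 to 0.3, and 61% even at correlation 0. The conclusion depends on the article's means, SD, alpha and group sizes. The exact percentage also depends on what the SD refers to and on correlations that the article does not give.

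**What to change.** Keep 105 patients. In the Sample size section:
- State that 96 gives 81% power for the three-group omnibus test.
- Give power and detectable difference for each planned comparison: acupuncture versus wait-list, saying whether one or both acupuncture arms are meant, and with versus without deqi.
- State the assumptions used: whether SD 10 is for the change or the raw score, which time point or average is tested, and any correlation.

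In the analysis section, say that the deqi contrast will be reported as an estimated difference with its 95% CI and that non-significance will not be read as absence of an effect. Qualify the remark on stable power in the Discussion in the same way.

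The cost is wording and a less favourable stated power; no patient is added and the design does not change. The Trial status section reports 61 participants recruited with recruitment still open, so on that status the change can be made before the data are analysed.
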